**1.2.3.4. Non-clinical pharmacokinetics of Y-2 Sublingual Tablets**

To systematically elucidate the ADME of Y-2 Sublingual Tablets, pharmacokinetic studies of intravenous injection of edaravone, dexborneol, edaravone dexborneol, and sublingual administration of Y-2 Sublingual Tablets (or Y-2 solution) are summarized in this Section, including absorption, distribution, metabolism and excretion of intravenous injection of edaravone dexborneol, edaravone and dexborneol in rats; distribution and excretion of Y-2 solution (Considering that it was not easy to administrate Y-2 Sublingual Tablets in rats, sublingual administration of Y-2 solution was given for the study of tissue distribution and excretion) in rats; pharmacokinetic study of single dose or 7-day repeated doses of intravenous administration of edaravone dexborneol, edaravone, dexborneol and sublingual administration of Y-2 Sublingual Tablets in dogs; bridging pharmacokinetic study of intravenous administration of edaravone dexborneol and sublingual administration of Y-2 Sublingual Tablets in dogs; plasma protein binding rate; metabolism of edaravone and dexborneol; inhibition of edaravone dexborneol and dexborneol on major hepatic CYPs in humans and induction on hepatic CYPs in rats.

**PK and absorption**

In rats, after single intravenous injection of edaravone at doses of 0.6, 1.2, 2.4, or 7.2 mg/kg, the edaravone  $t_{1/2}$  was 0.57, 1.54, 1.49, or 1.76 h, respectively, and the edaravone  $AUC_{0-inf}$  was 827.7, 2,383.5, 3,878.7, or 10,759.9 ng·h/mL, respectively. After single intravenous injection of dexborneol at dose of 0.15, 0.3, 0.6, or 1.8 mg/kg, the dexborneol  $t_{1/2}$  in all dose groups was less than 30 minutes, and the dexborneol  $AUC_{0-inf}$  was 12.5, 31.1, 65.9, or 194.0 ng·h/mL, respectively. After single intravenous injection of edaravone dexborneol (4:1) at doses of 0.75, 1.5, 3.0, or 9.0 mg/kg, the edaravone  $t_{1/2}$  was 0.59, 1.48, 1.42, or 1.71 h, respectively, and the edaravone  $AUC_{0-inf}$  was 784.6, 2,103.4, 3,636.2, or 11,743.0 ng·h/mL, respectively; the dexborneol  $t_{1/2}$  in all dose groups was less than 30 minutes, and the dexborneol  $AUC_{0-inf}$  was 18.8, 38.1, 73.3, or 246.6 ng·h/mL, respectively. The edaravone and dexborneol exposure ( $AUC_{0-inf}$ ) following the intravenous injection of edaravone, dexborneol, or edaravone dexborneol was proportional to dose increase. The dexborneol and edaravone in edaravone dexborneol had no effect on the PK properties of either dexborneol or edaravone.

In dogs, after single intravenous injection of edaravone at doses of 2.4, 4.8, or 9.6 mg/kg, the edaravone  $t_{1/2}$  was 8.79, 9.63, or 9.57 h, respectively, and the edaravone  $AUC_{0-inf}$  was 30,977.6, 51,648.3, or 65,479.8 ng·h/mL, respectively. After single intravenous injection of dexborneol at doses of 0.6, 1.2, or 2.4 mg/kg, the dexborneol  $t_{1/2}$  was 0.64, 0.90, or 0.92 h, respectively, and the dexborneol  $AUC_{0-inf}$  was 99.8, 197.9, or 501.2 ng·h/mL, respectively. After single intravenous injection of edaravone dexborneol (4:1) at doses of 0.75, 1.5, 3.0, or 9.0 mg/kg, the edaravone  $t_{1/2}$  was 9.48, 9.55, or 9.97 h, respectively, and the edaravone  $AUC_{0-inf}$  was 28,341.4, 48,593.2, or 60,077.6 ng·h/mL, respectively; the dexborneol  $t_{1/2}$  was 0.67, 0.86, or 1.05 h, respectively, and the dexborneol  $AUC_{0-inf}$  was 114.9, 207.3, or 432.1 ng·h/mL, respectively. After 7-day repeated intravenous injection of edaravone (4.8 mg/kg), dexborneol (1.2 mg/kg), or edaravone dexborneol (6 mg/kg, 4:1), the edaravone  $t_{1/2}$  was 8.65, N/A, or 8.13 h, respectively, and the edaravone  $AUC_{0-inf}$  was 45,906.9, N/A, or 41,614.2 ng·h/mL, respectively; the dexborneol  $t_{1/2}$  was N/A, 1.33, or 1.4 h, and the dexborneol  $AUC_{0-inf}$  was N/A, 298.8, or 248.2 ng·h/mL, respectively. The cumulative coefficient ( $AUC_{0-inf}$  ratio from Day 7 to Day 1) of dexborneol in dexborneol and edaravone dexborneol was 1.51 and 1.20, respectively, and the cumulative coefficient of edaravone in edaravone and edaravone dexborneol was 0.89 and 0.86, respectively. A dose-dependent increase in mean dexborneol  $AUC_{0-inf}$  was observed in dogs following single or repeated 7-day administration, whereas not detected in the high-dose edaravone group. In the experiment of single dose or 7-day repeated doses, there was no significant difference in the PK properties of edaravone and dexborneol in edaravone, or dexborneol and edaravone dexborneol. The dexborneol and edaravone in edaravone dexborneol had no effect on the PK properties of either dexborneol or edaravone.

In the bridging pharmacokinetic study of sublingual administration of edaravone dexborneol (5:1) and intravenous injection of edaravone dexborneol (4:1), after intravenous injection of edaravone dexborneol (30 mg, including 24 mg edaravone and 6 mg dexborneol) or sublingual administration of Y-2 Sublingual Tablets (1 tablet, 36 mg, including 30 mg edaravone and 6 mg dexborneol), edaravone and dexborneol showed similar pharmacokinetic parameters ( $C_{max}$ ,  $AUC_{0-t}$ ,  $AUC_{0-inf}$ ,  $t_{1/2}$ , MRT) in male and female dogs. After single

administration of Y-2 Sublingual Tablets (1 tablet), the  $t_{\max}$  of edaravone and dexborneol was 0.63 h and 0.35 h, respectively, and the bioavailability was 70% and 85%, respectively.

After single administration of 36 mg (1 tablet) of Y-2 Sublingual Tablets, 72 mg (2 tablets), or 108 mg (3 tablets), the edaravone exposure ( $C_{\max}$  and  $AUC_{0-\infty}$ ) increased in a dose-dependent manner. No gender differences were observed for any of the pharmacokinetic parameters, except for inter-individual variations in  $C_{\max}$  (♂89.5 ng/mL vs ♀211 ng/mL) and  $AUC_{0-\infty}$  (♂58.2 ng·h/mL vs ♀110 ng·h/mL) of dexborneol in the 36 mg Y-2 (1 tablet) dose group, which may be due to the limited number of animals (3 males and 3 females). After 7-day repeated doses of 72 mg (2 tablets) of Y-2 Sublingual Tablets, the mean  $AUC_{0-\infty}$  of edaravone and dexborneol on Day 7 was approximately 1.17 and 1.05 times that on Day 1, respectively, indicating that multiple doses had no accumulation potential.

### **Distribution**

#### **Plasma protein binding rate**

The in vitro plasma protein binding rates of edaravone and dexborneol were approximately 70% and 69% in rats, 35% and 77% in dogs, and 75.5% and 68% in humans, respectively. The plasma protein binding rate of edaravone showed species difference and reached saturation at 50,000 ng/mL. No drug interactions were found in the plasma protein binding rates of edaravone and dexborneol.

#### **Tissue distribution**

Tissues were collected 5 min, 20 min, or 2 h after intravenous injection of edaravone (2.4 mg/kg), dexborneol (0.6 mg/kg), or edaravone dexborneol (3.0 mg/kg, 4:1) for a comparative study of tissue distribution. The study showed that edaravone or dexborneol had no effect on the tissue distribution of each other in rats.

In SD rats, after single intravenous injection of edaravone dexborneol (6 mg/kg, 4:1) or single sublingual administration of dexborneol (6 mg/kg, 5:1, i.e., Y-2 solution), edaravone and dexborneol were rapidly distributed and cleared in each tissue. After intravenous or sublingual administration, edaravone was higher in liver and kidney, while dexborneol was higher in kidney, brain, and adipose tissue. Edaravone and dexborneol had no significant accumulation in important tissues. There was no significant distribution difference in

important tissues such as heart, liver, spleen, lung, kidney, and brain after intravenous injection of edaravone dexborneol (4:1) and sublingual administration of edaravone dexborneol (5:1).

## **Metabolism**

### **In vitro biotransformation**

In vitro primary biotransformation of dexborneol to glucuronic acid conjugation and forming of glucuronic acid conjugate (B-M1) is identical in all species (mice, rats, dogs, monkeys, and humans), which can also be detected in vivo. None of the recombinant human CYPs or UGTs systems constructed in vitro, including rCYP1A2, 2B6, 2C8, 2C9, 2C19, 2D6 or 3A4 and rUGT1A1, 1A3, 1A4, 1A6, 1A9, 2B7 or 2B15, and other metabolic enzymes were involved in the glucuronic acid conjugation of dexborneol.

### **In vivo metabolism**

The Phase II metabolites of edaravone, glucuronic acid conjugate (E-M1) and sulfate conjugate (E-M2), were detected in urine and bile samples of rats after intravenous injection of edaravone dexborneol (edaravone (2.4 mg/kg) and dexborneol (0.6 mg/kg)). Glucuronic acid conjugate (B-M1) of dexborneol was detected in urine and bile samples, and traces of camphor (B-M2) were detected in plasma in toxicokinetic study. No other metabolites of edaravone or dexborneol were found in rats. Data from the clinical review of Radicava® (edaravone injection, FDA, NDA 209176) showed that the metabolic properties of edaravone were similar in Japanese and Caucasian populations, with sulfate followed by glucuronic acid conjugate being major metabolites in plasma and glucuronic acid conjugate followed by sulfate being major metabolites in urine.

## **Excretion**

In rats, after single intravenous injection of edaravone (2.4 mg/kg) or edaravone dexborneol (edaravone (2.4 mg/kg) and dexborneol (0.6 mg/kg)), the 72-hour cumulative urinary excretion rate of edaravone was 51.8% and 47.9%, respectively. The 24-hour cumulative bile excretion rate of edaravone and glucuronic acid conjugate was 28.6% and 34.6%, respectively. No edaravone or glucuronic acid conjugate was detected in fecal samples. There was no significant difference in the excretion rate of edaravone after administration of

edaravone and edaravone dexborneol. Dexborneol had no significant effect on the excretion of edaravone.

After single intravenous injection of dexborneol (0.6 mg/kg) or edaravone dexborneol (3 mg/kg, including edaravone (2.4 mg/kg) and dexborneol (0.6 mg/kg)), the 72-hour cumulative urinary excretion rate of dexborneol was 12.1% and 15.1%, respectively; the 4-hour cumulative bile excretion rate was 0.043% and 0.029%, respectively, and the 72-hour cumulative fecal excretion rate of was 8.3% and 6.1%. There was no significant difference in the excretion rate of dexborneol in animals administered with dexborneol or edaravone dexborneol.

After single sublingual administration of edaravone dexborneol (6.0 mg/kg, including edaravone (5 mg/kg) and dexborneol (1 mg/kg)), edaravone was excreted mainly in the urine in the form of proto type and glucuronic acid conjugate (E-M1). The 72-hour total cumulative excretion rate of edaravone and glucuronic acid conjugate was about 29%. Dexborneol was excreted mainly in urine and bile as glucuronic acid conjugate (B-M1) and in feces as proto type. The total cumulative excretion rate of dexborneol and B-M1 was about 35.7%.

### **Pharmacokinetic drug interactions**

#### **CYP inhibition and induction**

The results of in vitro enzymatic study showed that edaravone, dexborneol, and edaravone dexborneol (4:1) had no significant inhibitory effect on five major CYP450 subtypes (CYP1A2, CYP2C9, CYP2C19, CYP2D6, and CYP3A4). The IC50 of the three drugs was all  $\geq 100$   $\mu$ M. At the animal level, respective intravenous injection of the three drugs did not induce CYP1A2, CYP2C9, CYP2C19, and CYP3A4 in SD rats.

#### **1.2.3.5. Clinical pharmacokinetics**

The Phase I clinical study of Y-2 Sublingual Tablets was conducted in healthy adult participants. The study was divided into single-ascending dose trial (1 tablet, 2 tablets, and 3 tablets, 10 participants in each group) and multiple-ascending dose trial (1 tablet, 2 tablets, 10 participants in each group) to evaluate the safety, tolerability and pharmacokinetic profile of Y-2 Sublingual Tablets in healthy adult male and female participants.

After single sublingual administration of Y-2 Sublingual Tablets at dose of 1 tablet (containing 30 mg of edaravone + 6 mg of dexborneol), 2 tablets (containing 60 mg of edaravone + 12 mg of dexborneol), and 3 tablets (containing 90 mg of edaravone + 18 mg of dexborneol), edaravone and dexborneol were absorbed rapidly in the body. With the increase of dose, the  $C_{\max}$  and exposure AUC of edaravone in plasma increased accordingly; The increase of  $C_{\max}$  showed a rough but atypical dose-proportional increase, and the exposure  $AUC_{\text{last}}$  and  $AUC_{\text{inf}}$  did not show a typical dose-exposure proportional relationship, with an increase slightly greater than the proportional increase in dose. With the increase of the administered dose, dexborneol in plasma did not increase significantly, showing a saturated trend; In the dose range of 6-18 mg,  $C_{\max}$  and AUC did not show a dose-exposure proportional relationship, both of which were less than the proportional increase of dose.

After Y-2 Sublingual Tablets was administered twice a day (BID) for 9 consecutive days at dose of 1 tablet (containing 30 mg of edaravone + 6 mg of dexborneol) and 2 tablets (containing 60 mg of edaravone + 12 mg of dexborneol), edaravone and dexborneol in plasma basically reached a stable state. After continuous administration, there was no significant accumulation of edaravone and dexborneol in plasma, and the AUC accumulation ratios of edaravone and dexborneol exposure were  $1.05 \pm 0.0995$  (0.708~1.19) and  $1.35 \pm 0.364$  (0.596~1.85), respectively.

A total of 33 adverse events and 4 adverse reactions occurred during the single-dose and multiple-dose trial. The incidence of adverse events and adverse reactions was not dose-dependent, and the outcome of adverse reactions was either remission of symptoms or return to baseline levels.

Table 1.2-4. Pharmacokinetic Parameters of Edaravone in Healthy Adult Participants after Single Administration of Y-2 Sublingual Tablets

| PK parameter               | 1 tablet  | 2 tablets  | 3 tablets  |
|----------------------------|-----------|------------|------------|
|                            | N=10      | N=10       | N=10       |
| $AUC_{0-\infty}$ (h*ng/mL) | 5290±2080 | 13200±3970 | 20500±3900 |
| $AUC_{0-t}$ (h*ng/mL)      | 5160±2040 | 13000±3970 | 20300±3910 |

|                           |                   |                   |                   |
|---------------------------|-------------------|-------------------|-------------------|
| $C_{\max}$ (ng/mL)        | 2110±756          | 4270±1320         | 6330±1070         |
| $t_{1/2}$ (h)             | 2.87±0.67         | 3.64±0.61         | 3.67±0.51         |
| $T_{\max}$ (h) (Min, Max) | 1.00 (0.75, 1.00) | 1.00 (1.00, 2.00) | 1.25 (0.75, 1.50) |
| $V_z/F$ (L)               | 25.8±8.08         | 25.3±5.85         | 23.9±5.69         |
| $CL/F$ (L/h)              | 6.54±2.51         | 5.00±1.68         | 4.55±0.95         |

Table 1.2-5. Pharmacokinetic Parameters of Dexborneol in Healthy Adult Participants after  
Single Administration of Y-2 Sublingual Tablets

| PK parameter               | 1 tablet          | 2 tablets         | 3 tablets           |
|----------------------------|-------------------|-------------------|---------------------|
|                            | N=10              | N=10              | N=10                |
| $AUC_{0-\infty}$ (h*ng/mL) | 30.8±12.1         | 36.1±9.89         | 49.6±15.9           |
| $AUC_{0-t}$ (h*ng/mL)      | 26.7±12.9         | 31.9±12.4         | 46.5±15.0           |
| $C_{\max}$ (ng/mL)         | 20.0±8.61         | 24.4±11.5         | 35.1±19.9           |
| $t_{1/2}$ (h)              | 2.40±1.71         | 1.64±0.537        | 3.16±0.895          |
| $T_{\max}$ (h) (Min, Max)  | 0.50 (0.25, 0.75) | 0.50 (0.50, 1.00) | 0.625 (0.167, 0.75) |
| $V_z/F$ (L)                | 738±561           | 888±504           | 1720±382            |
| $CL/F$ (L/h)               | 226±95.2          | 366±145           | 399±128             |

Table 1.2-6 Pharmacokinetic Parameters of Edaravone in Healthy Adult Participants after  
Multiple Administration

| PK parameter               | 1 tablet (first time) | 1 tablet (last time - 9th time) |
|----------------------------|-----------------------|---------------------------------|
|                            | N=10                  | N=10                            |
| $AUC_{0-t}$ (h*ng/mL)      | 6170±2550             | 7000±3330                       |
| $AUC_{0-\infty}$ (h*ng/mL) | 6500±2810             | 7130±3360                       |
| $AUC_{0-12h}$ (h*ng/mL)    | 6170±2550             | 6510±2830                       |
| $C_{\max}$ (ng/mL)         | 2470±840              | 2520±721                        |
| $t_{1/2}$ (h)              | 2.89±0.46             | 3.76±1.03                       |
| $T_{\max}$ (h) (Min, Max)  | 1.00 (0.75, 2.00)     | 1.00 (0.50, 1.00)               |
| $V_z/F$ (L)                | 21.8±7.72             | 27.0±8.26                       |
| $CL/F$ (L/h)               | 5.41±2.16             | 5.32±1.91                       |

|                                 |                        |                                  |
|---------------------------------|------------------------|----------------------------------|
| AUC accumulation index          |                        | 1.06                             |
| PK parameter                    | 2 tablets (first time) | 2 tablets (last time - 9th time) |
|                                 | N=10                   | N=10                             |
| AUC 0-t (h*ng/mL)    | 11200±2130             | 12600±2690                       |
| AUC 0-∞ (h*ng/mL)    | 11600±2270             | 12800±2720                       |
| AUC 0-12h (h*ng/mL)  | 11200±2130             | 11700±2390                       |
| C max (ng/mL)        | 4210±733               | 3950±686                         |
| t 1/2 (h)            | 2.49±0.24              | 4.36±0.34                        |
| T max (h) (Min, Max) | 1.00 (0.75, 2.00)      | 1.50 (1.00, 2.00)                |
| V z /F (L)           | 19.1±2.93              | 33.6±8.75                        |
| CL/F (L/h)                      | 5.36±1.05              | 5.31±1.10                        |
| AUC accumulation index          |                        | 1.04                             |

Table 1.2-7 Pharmacokinetic Parameters of Dexborneol in Healthy Adult Participants after  
Multiple Administration

|                                 |                       |                                 |
|---------------------------------|-----------------------|---------------------------------|
| PK parameter                    | 1 tablet (first time) | 1 tablet (last time - 9th time) |
|                                 | N=10                  | N=10                            |
| AUC 0-t (h*ng/mL)    | 22.5±8.47             | 42.7±14.2                       |
| AUC 0-∞ (h*ng/mL)    | 26.0±9.27             | 39.5±18.3                       |
| AUC 0-12h (h*ng/mL)  | 24.1±9.02             | 37.1±10.5                       |
| C max (ng/mL)        | 22.5±19.4             | 25.9±10.7                       |
| t 1/2 (h)            | 2.72±0.887            | 4.02±1.13                       |
| T max (h) (Min, Max) | 0.50 (0.50, 0.75)     | 0.25 (0.25, 0.50)               |
| V z /F (L)           | 988±396               | 1210±829                        |

|                                 |                        |                                  |
|---------------------------------|------------------------|----------------------------------|
| CL/F (L/h)                      | 260±98.2               | 176±61.1                         |
| AUC accumulation index          |                        | 1.54                             |
| PK parameter                    | 2 tablets (first time) | 2 tablets (last time - 9th time) |
|                                 | N=10                   | N=10                             |
| AUC 0-t (h*ng/mL)    | 36.6±11.4              | 51.9±18.8                        |
| AUC 0-∞ (h*ng/mL)    | 40.2±12.9              | 64.8±28.5                        |
| AUC 0-12h (h*ng/mL)  | 39.0±13.1              | 45.3±14.3                        |
| C max (ng/mL)        | 23.7±13.3              | 26.2±15.2                        |
| t 1/2 (h)            | 4.01±1.66              | 7.90±4.12                        |
| T max (h) (Min, Max) | 0.75 (0.25, 1.00)      | 0.50 (0.50, 0.75)                |
| V d /F (mL)          | 1710±376               | 2727±1169                        |
| CL/F (mL/h)                     | 325±93.1               | 284±71.6                         |
| AUC accumulation index          |                        | 1.25                             |

### 1.3. Risk

Based on the available evidence, this product has potential clinical efficacy in improving prognostic neurological function in patients with acute ischemic stroke. It was confirmed in the phase III trial (SIM-23-02 trial) that the clinical efficacy of concentrated solution of edaravone dexborneol for injection, which has similar active ingredients of this product, was significantly superior to that of edaravone injection. The results of the SIM-23-02 trial showed that the proportion of participants with mRS score  $\leq 1$  on Day 90 in the group of concentrated solution of edaravone dexborneol for injection (65.61%) was much higher than that in the group of edaravone injection (57.48%). The difference between the two groups was 8.13%, and the 95% CI was (2.63% ~ 13.63%, P = 0.0039). The mean differences from baseline in NIHSS scores were -2.97, -3.99, and -4.81 respectively on days 14, 30, and 90 after treatment in the edaravone dexborneol group, and -2.56, -3.60, and -4.49 respectively in the edaravone group. The differences from baseline were statistically significant in both

groups. The mean differences of decrease in NIHSS scores between the edaravone dexborneol group and the edaravone group on days 14, 30, and 90 were -0.41 (95%CI: -0.73~ -0.09,  $P = 0.0097$ ), -0.39 (95%CI: -0.71~ -0.07,  $P = 0.0151$ ), and -0.32 (95%CI: -0.64 ~ -0.01,  $P = 0.0370$ ), respectively. The differences between the two groups were statistically significant.

When edaravone was approved for marketing in Japan, clinical trials showed that there were 26 cases (4.57%) of adverse reactions in 569 cases in total, and the main adverse reactions were liver dysfunction in 16 cases (2.81%), allergy in 6 cases (1.05%), and rash in 4 cases (0.70%). Among the 569 cases, 122 (21.4%) were considered to have laboratory abnormalities, mainly including increased AST (GOT) (43/558 cases: 7.71%), increased ALT (GPT) (46/559 cases: 8.23%), and other abnormal liver function test.

In the more than 2 years since the launch of edaravone in Japan, the number of patients treated with edaravone in Japan was about 310,000, and 162 cases of acute renal insufficiency (0.052% of users) were reported, including cases with unknown causality. The occurrence time of adverse reactions showed that 155 of 162 cases had clear occurrence time, of which 85 cases occurred within 7 days after administration and reached the peak 4 days after administration. Hishida reported that among 207 patients with renal dysfunction during the administration of edaravone, 8.2% of the cases with renal insufficiency was highly related to the administration of edaravone and 34.8% of that was possibly related.

A monitoring study of adverse reactions conducted by the regulatory authority of Mitsubishi Pharmaceutical found that the incidence of edaravone related liver dysfunction was 4.3% and edaravone was considered a possible cause of renal dysfunction. Fulminant hepatitis was a serious drug-related adverse reaction of edaravone recently observed. According to statistics, 7 cases of fulminant hepatitis reported in Japan from April 2003 to February 2007 were related to the clinical application of edaravone.

According to all serious adverse reactions reported, although some serious adverse reactions are extremely rare, edaravone still adds new safety warnings, including granulocytopenia, acute lung disease, rhabdomyolysis, and hepatitis. In the revision of the 14th edition in 2009, the instructions for edaravone injection in Japan listed 7 serious adverse reactions: 1. acute renal failure, nephrotic syndrome; 2. fulminant hepatitis, liver failure,

jaundice; 3. thrombocytopenia, granulocytopenia; 4. diffuse intravascular coagulation (DIC); 5. acute lung injury; 6. rhabdomyolysis; 7. shock. allergic reactions.

Wang Wei et al. analyzed the adverse reactions of 8,645 patients by using computers to search Pubmed, SinoMed and references of the literature obtained, and comprehensively analyzed the safety of edaravone by applying meta-analysis in randomized controlled trials of edaravone in the treatment of acute cerebral infarction. The results showed that the most common adverse reactions of edaravone were mildly increased aminotransferase and abnormal renal function, with adverse reactions (283 cases) accounting for 3.27% of the total number (8,645 cases); A total of 10 randomized controlled trials of edaravone in the treatment of acute cerebral infarction was included in the meta-analysis, and the results showed that there was no statistically significant difference in the incidence of adverse events, increased aminotransferase, and abnormal renal function between the edaravone + conventional treatment group and the conventional treatment group. It has been proved that the incidence of adverse reactions of edaravone is very low in China and its clinical application is safe.

According to the current reports of serious adverse reactions, there are also some extremely rare serious adverse reactions, including granulocytopenia, acute lung disease, rhabdomyolysis, and hepatitis. In the revision of the 14th edition in 2009, the instructions for edaravone injection in Japan listed 7 serious adverse reactions: 1. acute renal failure, nephrotic syndrome; 2. fulminant hepatitis, liver failure, jaundice; 3. thrombocytopenia, granulocytopenia; 4. diffuse intravascular coagulation (DIC); 5. acute lung injury; 6. rhabdomyolysis; 7. shock. allergic reactions.

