## **8.5. Safety analysis**

Data for safety evaluation include adverse events observed during the study and changes in laboratory data before and after treatment. Adverse event data are processed in statistical analysis after encoding according to the current version of MedDRA at the time of encoding.

Adverse events, adverse events during the study period since the first dose of the drug, major adverse events, unexpected adverse events, adverse event of special interest, serious adverse events, adverse events related to study drugs and serious adverse events related to study drugs are classified by system organ class and preferred term. Among them, significant adverse events are defined as adverse events that require drug therapy or non-drug therapy for the subject reporting the event; adverse events of special interest are divided into three types, i.e., liver function impairment, renal function impairment and hypokalemia. The Sponsor's clinical research associate is responsible for confirming and classifying all adverse events before unblinding.

If multiple adverse events occur in the same subject, the incidence rate is counted as 1 case; When the same AE occurs multiple times, the incidence of this AE is counted as 1. Adverse events will be summarized in frequency tables according to the system organ class (SOC) and preferred term (PT). The incidence is calculated by system, symptom/sign (count of cases: number of subjects who have experienced at least one adverse event).

The list of subjects experiencing adverse events and the list of subjects experiencing SAEs are provided. With respect to the laboratory data, in addition to the mean comparison before and after treatment, details of cases that are normal before treatment and abnormal after treatment or cases with abnormalities before treatment and abnormality exacerbation after treatment are mainly analyzed and listed. Refer to the statistical analysis plan for other details.

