### 4.4.2 Adverse Events

Adverse event data will be coded according to the current version of MedDRA. Treatment Emergent Adverse Event (TEAE) will be used in the analysis, while adverse events that start prior to the first dose of study medication (pre-treatment) will not be involved into the safety

analysis. Adverse events on study medication (during treatment) and after the last dose of study medication (post-treatment) will be analyzed.

The differences in the proportions of patients with AE between treatment groups and their corresponding 95% CIs will be estimated based on Newcombe–Wilson. The ORs and 95% CIs will be estimated with the logistic regression. Chi-squared test or Fisher’s Exact test will be used to compare the number of each AE combination according to system organ class and preferred term between treatment groups.

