#### **4.4.3 Severe Adverse Events**

The differences in the proportions of patients with SAE between treatment groups and their corresponding 95% CIs will be estimated based on Newcombe–Wilson. The ORs and 95% CIs will be estimated with the logistic regression. Chi-squared test or Fisher’s Exact test will be used to compare the number of each SAE combination according to system organ class and preferred term between treatment groups.

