#### **4.4.4 Vital Signs and Laboratory Test Examination**

Within each treatment group, the number and percentage of subjects with elevated in vital signs from baseline to day 14 after randomization will be described and Fisher’s Exact test will be used to compare the difference between treatment groups. The baseline measurements and changes after treatment of blood routine and bloodbiochemistry will be described as "abnormal and clinically significant" will be determined by the researchers. Within each treatment group, the number and percentage of subjects with an "abnormal and clinically significant" value will be summarized and Fisher’s Exact test will be used to compare the difference between treatment groups.

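### Protocol 1.3 names seven groups of serious edaravone reactions, but only two of them are events of special interest, and the SAP analyses no special-interest event as a group; the clearest loss is for allergy and rash

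*Combined protocol and SAP*

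**What the plan says.** Protocol 1.3 (Risk) states that "the instructions for edaravone injection in Japan listed 7 serious adverse reactions". The first two are renal (acute renal failure, nephrotic syndrome) and hepatic (fulminant hepatitis, liver failure, jaundice). The other five are "3. thrombocytopenia, granulocytopenia; 4. diffuse intravascular coagulation (DIC); 5. acute lung injury; 6. rhabdomyolysis; 7. shock. allergic reactions". For the 569 cases behind the Japanese approval, the same section reports that "the main adverse reactions were liver dysfunction in 16 cases (2.81%), allergy in 6 cases (1.05%), and rash in 4 cases (0.70" percent).

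Protocol 8.5 then fixes the special-interest list: "adverse events of special interest are divided into three types, i.e., liver function impairment, renal function impairment and hypokalemia". Hypokalemia does not appear in 1.3. Protocol 8.5 classifies these events by organ class and preferred term, as it does the other adverse event categories, and refers to the SAP for further detail. The SAP does not mention events of special interest.

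For adverse events, SAP 4.4.2 uses a chi-squared or Fisher test "to compare the number of each AE combination according to system organ class and preferred term between treatment groups". SAP 4.4.3 does the same for serious events: "to compare the number of each SAE combination according to system organ class and preferred term between treatment groups". Both sections also give the arm difference in patients with events, with a Newcombe-Wilson confidence interval and an odds ratio.

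On laboratory data, SAP 4.4.4 says: "The baseline measurements and changes after treatment of blood routine and bloodbiochemistry will be described". It compares clinically significant abnormal values between arms by Fisher's test. In protocol Table 7.2-1, platelets and neutrophils belong to blood routine and creatine kinase (CK) to blood biochemistry. Coagulation is a separate row of that table, and SAP 4.4.4 does not name it.

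**The concern.** Safety is half of the trial objective, and 1.3 sets out in advance which harms are expected of this drug class. A special-interest list exists so that such harms are counted as one clinical entity. Here five of the seven named groups are not on the list. The groups that are on it have no term list, no laboratory threshold and no between-arm analysis in the SAP.

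The gap matters most for allergic harm. An allergic reaction and a rash can be coded to different preferred terms and different organ classes, and each class also holds unrelated events. Neither planned level of comparison therefore forms a hypersensitivity count. A real excess on active drug could be divided between two or more small comparisons. Protocol 8.5 also leaves confirmation and classification of adverse events before unblinding to the sponsor's clinical research associate, so without a fixed list the grouping is open to discretion.

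**Working it through.** **Plan's own figure.** The documents give no power for any safety comparison, so the check starts from the arm size in protocol 8.1. With 50% against 40%, two-sided 0.05 and 80% power:

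n = [1.960·√(2·0.45·0.55) + 0.842·√(0.25 + 0.24)]² / 0.10² = (1.379 + 0.589)² / 0.01 ≈ 387.3, so 388; then 388 / 0.85 = 456.5, so 457.

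Both stated numbers reproduce. I use 457 per arm for safety and show 388 as a lower case.

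**Coverage, group by group.**

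| Group in 1.3 | Special interest (8.5) | Organ class and preferred term (SAP 4.4.2, 4.4.3) | Laboratory comparison (SAP 4.4.4) |
|---|---|---|---|
| Renal | yes | yes | yes (biochemistry) |
| Hepatic | yes | yes | yes (biochemistry) |
| Blood cells | no | yes | yes (platelets, neutrophils) |
| DIC | no | yes | platelets only; coagulation not named |
| Acute lung injury | no | yes | none |
| Rhabdomyolysis | no | yes | yes (CK) |
| Shock/allergic | no | yes | none |

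**Allergy and rash: inputs.**
- Active-arm rates from 1.3: allergy 6/569 = 1.05%, rash 4/569 = 0.70%, together 10/569 = 1.76%. Adding assumes no patient had both. That fits the section's own total, since 16 + 6 + 4 = 26 cases.
- Placebo rate for the two together: assumed 0%, 0.2% or 0.4%, divided 60:40 between allergy and rash.
- Test: two-sided Fisher at 0.05. Power is the sum of binomial probabilities over all tables with p ≤ 0.05 and more events on active.
- Chance that either separate test is significant: 1 − (1 − power for allergy)(1 − power for rash), treating the two as independent.

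**Threshold.** Against zero placebo cases, 5 v 0 gives p = 0.062 and 6 v 0 gives p = 0.031, so six cases are needed. Expected active-arm cases are 457 × 6/569 = 4.8 for allergy, 457 × 4/569 = 3.2 for rash and 8.0 pooled. Each separate count is expected to fall short of six; the pooled count is not.

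**Power, 457 per arm.**

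| Assumed placebo rate | Allergy alone | Rash alone | Either | Pooled |
|---|---|---|---|---|
| 0% | 35% | 11% | 42% | 81% |
| 0.2% | 24% | 8% | 30% | 58% |
| 0.4% | 16% | 6% | 21% | 39% |

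For example, at 0.2%: 1 − (1 − 0.242)(1 − 0.078) = 0.301. With 388 per arm the last two columns become 27% and 68%, 20% and 47%, and 14% and 31%.

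**Very rare groups.** Protocol 1.3 describes granulocytopenia, lung disease and rhabdomyolysis as extremely rare and gives no rate. At an assumed 0.1% against 0, a category has about 0.001% power; at 0.2%, 0.04%. What the trial can give is a bound: with 0 of 457, the one-sided 95% upper limit is 1 − 0.05^(1/457) = 0.65%.

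**The case against.** The strongest defence is that these harms are not ignored. Adverse and serious adverse events are tested by whole organ class as well as by preferred term. Any adverse event, any serious event and treatment-related events are compared as pooled outcomes. Platelets, neutrophils and CK get a between-arm laboratory test. Protocol 8.5 lists serious cases and laboratory shifts by subject, and 7.3.5 requires a causality assessment for each event. All of this stands. A reader who sees only the special-interest list might infer that the five groups are compared term by term and in no other way; SAP 4.4.2 to 4.4.4 do not support that.

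Second, special-interest status as written brings no grouped test: liver and renal events get none either. This also stands. The short list alone does not cause the loss of power; the missing grouped analysis in the SAP does, and lengthening the list without adding an analysis would change little.

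Third, a reader might infer that the planned comparisons have almost no power for any of these harms, for instance by spreading allergic events over four or more terms. The documents give two categories, allergy and rash, and no basis for a finer split. On those two, separate testing has 21% to 42% power, which is poor but not negligible.

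Fourth, the choice of liver and renal has support in 1.3, where a review of 8,645 patients found raised aminotransferase and abnormal renal function to be the most common reactions. Nothing obliges the trial to copy another product's label. That justifies the two groups chosen. It does not explain why allergy and rash, next after liver in the 569-case data, have no category.

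**Conclusion.** The point holds as a gap in grouping, not as an absence of comparison. Five of the seven groups in 1.3 have no prespecified grouped category, and no special-interest event, liver and renal included, has a grouped analysis in the SAP. For allergy and rash, one pooled category roughly doubles the chance of detecting an excess of the size in 1.3: 58% against 30% at a 0.2% placebo rate, within a range of 39% against 21% to 81% against 42%.

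These figures rest on assumptions the documents do not settle: the placebo rates and their 60:40 division, independence of the two separate tests, 457 analysed per arm, and transfer of reaction rates from edaravone cases to all-cause events on the sublingual combination. The calculation also leaves out the organ-class tests. The direction is the same at every placebo rate tried and at 388 per arm.

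For blood cells, DIC, lung injury and rhabdomyolysis, grouping would not give power to show an arm difference if they are as rare as 1.3 says. There the gain is a prespecified count with an interval. DIC has the further gap that coagulation results are collected but not named in SAP 4.4.4.

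**What to change.** 1. In protocol 8.5 and SAP 4.4.2, add a hypersensitivity/shock category that includes rash, defined by a list of preferred terms fixed before unblinding.
2. Define the existing liver and renal categories in the same way. For all three, count patients with at least one event and report the arm difference with the Newcombe-Wilson interval and odds ratio that SAP 4.4.2 already specifies.
3. For blood cells, DIC, lung injury and rhabdomyolysis, report prespecified counts with confidence intervals as descriptive estimates, stating that the trial is not powered to show an arm difference in them.
4. Name coagulation results in the SAP 4.4.4 comparison.

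The cost is the term lists, one more table and a few more estimates, to be labelled non-confirmatory. The data are already collected, and no visit, treatment or sample size changes. The minutes of the third IDMC meeting record agreement to lock the database. If allocation is already known, the table should be labelled as added after unblinding.
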